## Abstract

**Background:**

Cardiovascular disease is the leading cause of mortality worldwide, accounting for 13%-15% of all deaths. Cardiac rehabilitation has poor compliance and adherence. Telerehabilitation has been introduced to increase patients’ participation, access, and adherence with the help of digital technologies. The target group is patients with heart failure. A telerehabilitation program called “Future Patient” has been developed and consists of three phases: (1) titration of medicine (0-3 months), (2) implementation of the telerehabilitation protocols (3 months), and (3) follow-up with rehabilitation in everyday life (6 months). Patients in the Future Patient program measure their blood pressure, pulse, weight, number of steps taken, sleep, and respiration and answer questions online regarding their well-being. All data are transmitted and accessed in the HeartPortal by patients and health care professionals.

**Objective:**

The aim of this paper is to describe the research design, outcome measures, and data collection techniques in the clinical test of the Future Patient Telerehabilitation Program for patients with heart failure.

**Methods:**

A randomized controlled study will be performed. The intervention group will follow the Future Patient Telerehabilitation program, and the control group will follow the traditional cardiac rehabilitation program. The primary outcome is quality of life measured by the Kansas City Cardiomyopathy Questionnaire. Secondary outcomes are development of clinical data; illness perception; motivation; anxiety and depression; health and electronic health literacy; qualitative exploration of patients’, spouses’, and health care professionals’ experiences of participating in the telerehabilitation program; and a health economy evaluation of the program. Outcomes were assessed using questionnaires and through the data generated by digital technologies.

**Results:**

Data collection began in December 2016 and will be completed in October 2019. The study results will be published in peer-reviewed journals and presented at international conferences. Results from the Future Patient Telerehabilitation program are expected to be published by the spring of 2020.

**Conclusions:**

The expected outcomes are increased quality of life, increased motivation and illness perception, reduced anxiety and depressions, improved electronic health literacy, and health economics benefits. We expect the study to have a clinical impact for future telerehabilitation of patients with heart failure.

**Trial Registration:**

ClinicalTrials.gov NCT03388918; https://clinicaltrials.gov/ct2/show/NCT03388918

**International Registered Report Identifier (IRRID):**

DERR1-10.2196/14517

## Introduction

Cardiovascular disease is the leading cause of mortality [1-4], accounting for 13%-15% of all deaths worldwide and 24.8% of all deaths in Europe [3]. A majority of cardiovascular disease mortalities are caused by heart failure. Despite advances in heart failure treatment in the past decade, increased lifespan along with obesity and unhealthy lifestyle has caused a continuing increase in the prevalence of heart failure [4,5]. An increase in the prevalence combined with an increasing elderly population has increased the health care costs and the number of people with disabilities [6]. The rehabilitation of cardiac patients aims to improve patients’ recovery, functional capacity, psychosocial well-being, and quality of life by using interventions such as physical activity, improved diet, weight control, psychosocial coping, and disease management [3,7,8]. These kinds of lifestyle-based interventions are crucial for patient recovery. However, cardiac rehabilitation programs have poor compliance and adherence [3]. Patients may take their medication regularly, but they find it difficult to alter lifestyle routines. To address this problem, telerehabilitation has been introduced to increase patient participation, access, and adherence with the help of information and communication technology [3,9].

To date, telehealth and telerehabilitation in heart failure has focused on systems that use hemodynamic measurements (ie, blood pressure and pulse), respiration, weight, and subjective questions to assess the risks of worsening heart failure. The responses are sent to health care providers, who then act on these data. Generally, patients do not see their own data. Instead, they wait for a health care provider to communicate to them on whether their heart failure has worsened [10]. A review from 2014 concluded that telemonitoring of patients with heart failure helped minimize decompensation of heart failure in small, single-center use when providers and patients were dedicated or when communication was direct through structured telephone support. However, when telemonitoring was used for the care of populations (in large trials), it proved no better than conventional care [11]. When researchers used questionnaires and qualitative research designs to assess tailored telemonitoring in patients with heart failure, patients reported improved self-care abilities and self-efficacy [12-14].

Patients’ preferences and their choice of smart technology in telemonitoring have been assessed in a transatlantic multisite study [15]. Patients with heart failure (n=208) stated that they preferred mobile devices and self-tracking devices for monitoring everyday activity. The use of activity trackers in patients with heart failure had a motivational effect, helping patients increase the number of steps per day [3,16]. In some cases, monitoring daily activity can also be used as predictors of patient health. The Future Patient study [17] described here proposes a new approach in self-management of patients with heart failure by using self-tracking technologies for monitoring physical activity, sleep, respiration, and pulse at night by using low-cost, commercially available, Conformité Européene–marked trackers that can passively “observe” patients in everyday life and make data available for both patients and health care professionals. Based on participatory design [18-20], the Future Patient Telerehabilitation (FPT) program has been developed in collaboration with patients with heart failure; relatives; health care professionals from hospital and health care centers; companies; and an interdisciplinary research team comprising professionals from engineering, psychology, medicine, nursing, and organizational sociology.

The overall purpose of the FPT study is to develop a telerehabilitation program that helps increase the quality of life of patients with heart failure and educate them to perform individualized monitoring in order to detect worsening of their own symptoms, thereby avoiding rehospitalization. The FPT will be implemented and evaluated in a clinical trial. The aim of this paper is to describe the research design, outcome measures, and data collection techniques used in the Future Patient research project.

## Methods

### Future Patient Telerehabilitation Program

The FPT consist of three phases: (1) titration of medicine (0-3 months), (2) participation in the FPT at a health care center or call center (3 months), and (3) follow-up with rehabilitation in everyday life (6 months). The three phases of the telerehabilitation program are illustrated in Figure 1.

**Figure figure1:**
[figure not shown]
Telerehabilitation program in three steps.

### The HeartPortal

The HeartPortal is a digital toolbox that functions as an interactive learning module; the setup is illustrated in Figure 2, and screen captures are shown in Figure 3. The portal has been developed using a participatory design approach [19,21,22]. The HeartPortal consists of four elements:

**Figure figure3:**
[figure not shown]
Screen captures from the HeartPortal. (A) Front page for the patients. (B) Measurement from the pedometer. (C) The information platform. (D) An illustration of the patient-reported outcome.

An interactive information site for patient education, containing information on rehabilitation issues, presented in the form of text and short videos (1-1.5 minutes) with patients and relatives describing their experiences with heart failure, symptoms, living an everyday life with heart failure, etc.A communication platform enabling patients to communicate directly with health care professionals. The HeartPortal may be used by health care professionals and patients to collaborate on setting goals and activities, and the patients also have the opportunity to keep an online diary and define their own goals for rehabilitation.Visualization of measured values (blood pressure, day and night pulse, weight, respiration, steps, and hours slept).Patient-reported outcomes (PRO) data [23]. Every second week, patients complete an online questionnaire about their sleep patterns (Spiegel Sleep Questionnaire) [24]; well-being (three questions defined by the research group); and measures on physical limitations, symptoms, self-efficacy, social interaction, and quality of life using the validated Kansas City Cardiomyopathy Questionnaire (KCCQ) [25,26]. The aim of the PRO-data is to give patients and health care professionals a digital tool to evaluate the patient’s current status. The data are presented in the tracking module, thus enabling both patients and health care professionals to view the PRO in all phases of the FPT.

As part of the telerehabilitation program, there is continuous monitoring of the patient’s vital signs using technology-enabled devices/equipment. A list of the equipment used is provided below:

Blood pressure (UA 767PBT; A&D Medical, San Jose, CA) is measured every day during phase I.Weight scale (UC-321PBT; A&D Medical, Thebarton, South Australia, Australia) is used only in phase I of the FPT; in phases II and III, patients use their own weight scale. Patients with heart failure measure their weight every day during all three phases of the FPT.Data transmitter (QWH-HUB-V1.0E; Qualcomm Life, San Diego, CA) to help transfer data such as blood pressure, day pulse, and weight in a secure form from the devices and to the HeartPortal.Step counters (Fitbit Zip or Charge, San Francisco, CA). Patients with heart failure can decide what kind of stepcounter they want to use. Steps are measured every day and transmitted to the HeartPortal.Sleep sensor (Beddit 3, Espoo, Finland) measures the numbers of hours of sleep, night pulse, and respiration.A tablet (iPad Air 2, Cupertino, CA).

Figure 2 shows how data are presented in the HeartPortal. All the measured values are stored on a secure database at Aalborg University.

**Figure figure2:**
[figure not shown]
The context of the Future Patient study with the HeartPortal at the center.

The patients receive instructions on evaluating their own values and how to react if these values are abnormal. A telerehabilitation coordinator observes all the measured values as well, and during phase 1, the coordinator also acts as a coach, helping patients learn to observe and act on any abnormal readings or worsening of symptoms to avoid possible hospitalization. During phase II, health care professionals also view the data. All health care professionals from the hospital and health care centers have access to the data.

### Data and Network Security

There is a strong focus on data and network security in the Future Patient project due to the project’s complexity and the environment where data are generated from both the health system (pulled data) and the patients (pushed data). Based on different endpoints in the setup (patient’s home, workplace, health care center, etc), the technology used, and the classification of information, the formation of metadata will be addressed via reliable integration encryption and infrastructure reliability.

### Eligibility Criteria

The target group in this study consists of patients diagnosed with heart failure according to the New York Heart Association (NYHA) class I-IV [27]. Patients with heart failure are recruited from the Cardiology Wards at hospitals in Skive, Viborg, Silkeborg, and Randers, all situated in the central region of Jutland, Denmark. The inclusion criteria are that the patient must have had a heart failure–related hospitalization within the past 2 weeks; have a stable internet connection at home; and have the ability to sign an informed consent form. Patients may have a pacemaker, and a maximum of 20% of the target group may belong to NYHA class I. Exclusion criteria are a revascularization or open-heart surgery within 3 months prior to inclusion; presence of previous neurologic, musculoskeletal, or cognitive disability or active psychiatric history (as noted in the medical record) other than depression or anxiety related to cardiac or other chronic illness; and absence of basic Danish language skills. All data from the recruitment process and patient withdrawal or dropout will be documented in a consort diagram.

### Research Design

The FPT will be tested in a multicenter randomized controlled trial (RCT) using a mixed method [28] approach. The intervention group will participate in the FPT, while the control group will follow a traditional rehabilitation program at the health care center, which is structured according to the national cardiac rehabilitation guidelines [29]. Enrollment of patients began in December 2016, and the RCT will end in September 2019.

### Power Calculation

The sample size was defined based on a power calculation. The aim of this project is to increase the quality of life (QoL) using telerehabilitation compared to usual rehabilitation. Based on the official KCCQ guidelines [25], the power calculation estimated the number of participants needed to show an increase in QoL on a scale of 0-100. When using the KCCQ, a “moderate” improvement is equal to a 10-point increase. The target group in the study includes patients with heart failure of a severe degree. As such, a 10-point improvement in the KCCQ will denote a change in the quality of life for the individual patient. Assuming normal distributions and a power of 80%, the number of participants in each group should be 63. However, accounting for 10% dropout, the total number of patients needed for this study is 140. Hence, we plan to enroll 70 patients with heart failure in the intervention group and 70 patients with heart failure in the control group.

### Theoretical Framework

The FTP program was designed using the self-determination theory (SDT) as a theoretical starting point. With the goal of increasing the effectiveness of behavior change interventions [30], SDT offers a framework for understanding the role of individualization in motivation. In particular, SDT highlights how fulfillment of basic needs such as autonomy, competency, and relatedness are necessary for initiating and maintaining changes in lifestyle and health behavior over time [31]. If motivation is sustained only by external factors, the patient will not have sufficient incentive to self-regulate and independently maintain a healthy lifestyle. However, if the patient finds that their health behavior goals are in accordance with their own internal values and beliefs (autonomy), the patient will feel that he/she possesses sufficient knowledge and skills to achieve this health behavior successfully (competency) and will feel supported by others (relatedness). The patient will, in turn, experience intrinsic motivation, that is, motivation based on internal factors enabling the patient to maintain the required lifestyle and health behavior over time [31].

### Ethics

The Future Patient project has been approved by the Regional Ethics Committee (N-20160055) and the Danish Data Protection Agency. The study is listed in listed in ClinicalTrials.gov (NCT03388918). The study is being carried out in accordance with the Helsinki Declaration, and all participants have signed an informed consent form prior to enrollment in the study.

### Baseline Data

Baseline data on demographics, clinical status, primary and secondary diagnosis, NYHA class, and actual prescribed medicines are being collected for both the intervention and control groups (Table 1). Questions on smoking, alcohol consumption, physical activity, IT competences, and rehabilitation will be asked in both groups in the RCT as well.

### Outcome Measures

Primary and secondary outcome measures as well as the dates when they the data will be collected are shown in Table 1. The data collection process is described below.

### Quality of Life

QoL is the primary outcome, which is measured using the KCCQ [25]. KCCQ is a 23-item self-administered questionnaire and includes different clinical domains such as physical limitations, symptoms, self-efficacy, social interaction, and quality of life. The score is calculated by assigning an ordinal value to each response, beginning with 1, and then adding up to make up a scaled score for each domain. Missing responses are assigned a value corresponding to an average of the answered items within the domain. Scale scores are transformed into a 0-100 range. In the intervention group, the QoL is measured at baseline and then every second week throughout the duration of the program. In the control group, QoL is measured at baseline, 6 months, and 12 months.

### Progression in Clinical data

All measured clinical data including weight, blood pressure, pulse (day/night), steps, sleep, and respiration in the intervention group will be collected and analyzed.

### Illness Perception

Changes in illness perceptions are being evaluated for both groups using the Brief Illness Perception Questionnaire (Brief IPQ) [32]. The Brief IPQ is a nine-item scale questionnaire designed to rapidly assess the cognitive and emotional representations of illness. Five of the items assess cognitive illness representation, two items assess emotional representation, and one item assesses illness comprehension. The last item is a causal question that asks the patient to list the three most causal factors in their illness. All items except one, the causal question, are scored on a scale from 0 to 10. The measure of the Brief IPQ is compared between groups at baseline, 6 months, and 12 months.

### Type of Motivation

Changes in the type of motivation are measured using the Health Climate Change Questionnaire (HCCQ) [33]. The HCCQ is a 15-item questionnaire that assesses patients’ perceptions of the degree to which their health care providers are supportive of their autonomy. Respondents rate each statement on a seven-point Likert scale (from “Not at all true” to “Very true”). The total score is calculated by averaging the values of each item. The HCCQ can be used in its full version (15-items) or short version (6-items). In this study, the full version is used. The scores from HCCQ are compared between groups at baseline, 6 months, and 12 months.

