### Statistical Analysis

At baseline, descriptive statistics [39] will be reported as median with 25th-75th percentiles in the case of skewed distribution or mean (SD) for normally distributed continuous variables. The nonparametric Kolmogorov-Smirnov test will be used to investigate normality of the distribution. An intention-to-treat analysis on all the randomized subjects will be conducted to provide unbiased comparisons between the intervention and control groups in order to avoid the effects of dropout.

The analysis of change in QoL, anxiety and depression, self-determination, illness perception, type of motivation, and health and eHealth literacy tests will be performed using data acquired through questionnaires. Comparison of incidence rates will be used to investigate the differences between the intervention and control groups. Two-sided tests and a significance level of 0.05 will be used.

All events from the day after randomization to patient exit will be included, while any other evident outcomes will be measured as changes from baseline to all assessment time points. Changes in the other evident outcomes will be tested using linear mixed models. Linear mixed models allow repeated measures to be collected in a longitudinal design and are superior when dealing with dropouts compared to other methods used for repeated measures. Hence, it will not be necessary to use imputation techniques on missing data. Statistical analyses will be performed using SPSS [computer software] (version 25.0. Armonk, NJ: IBM Corp), and values of *P*<.05 will be considered significant for all tests.

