### Conclusions

The expected outcomes are increased quality of life, increased motivation and illness perception, reduced anxiety and depressions, improved eHealth literacy, and health economics benefits. We expect the study to have a clinical impact for future telerehabilitation of patients with heart failure.

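### The outcome labelled type of motivation is measured by a scale of perceived provider autonomy support, so it cannot by itself support the expected increase in motivation

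*Protocol article*

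**What the plan says.** The protocol article, under Type of Motivation, assigns the outcome to one instrument: "Changes in the type of motivation are measured using the Health Climate Change Questionnaire (HCCQ". The next sentence says that the 15-item scale "assesses patients’ perceptions of the degree to which their health care providers are supportive of their autonomy". On scoring: "The total score is calculated by averaging the values of each item". On the comparison: "The scores from HCCQ are compared between groups at baseline, 6 months, and 12 months".

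Table 1 carries type of motivation as a secondary outcome for both groups at baseline, 6 and 12 months. The Statistical Analysis section lists the questionnaire outcomes to be analysed for change, among them "anxiety and depression, self-determination, illness perception, type of motivation", so self-determination and type of motivation appear there as separate items. The Conclusions, and the conclusions of the abstract, list "increased motivation and illness perception" among the expected outcomes.

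**The concern.** The outcome's name and the description of its instrument refer to different things. Type of motivation is a property of the patient. Perceived autonomy support is the patient's judgement of the people providing care. If the plan is followed as written, a between-group difference on the HCCQ will be reported under the heading of motivation and read as the expected increase.

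The label matters because motivation is the route by which the program is meant to change behaviour (Theoretical Framework), and the Discussion names the use of self-determination theory as one of two areas in which the study is unique. A mislabelled scale would appear to confirm that route without having measured it.

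**Working it through.** No figure in the article bears on this point and no arithmetic applies. The check sets the sections side by side.

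1. **Construct against content (Type of Motivation).** The first sentence names change in type of motivation. The second describes patients' ratings of provider support. Nothing in the description refers to the patient's own reasons for acting, or to how strongly the patient is motivated.

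2. **Scoring (same section).** Fifteen seven-point items are averaged to one total. No subscales are described. To speak of a *type* of motivation, the score must at least distinguish motivation driven from within from motivation driven from outside. A single mean cannot do so, whatever the items contain.

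3. **The article's own theory (Theoretical Framework).** Motivation is treated there as a state of the patient: intrinsic if it rests on internal factors, as opposed to being sustained only by external ones. Autonomy, competency and relatedness are needs whose fulfilment leads in turn to intrinsic motivation, and feeling supported by others belongs to relatedness. Support from providers therefore stands before motivation in the chain. Using it as the motivation outcome assumes the step that would have to be shown.

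4. **Another explanation for a difference (The HeartPortal and the text following Figure 2).** The intervention group gets a platform for communicating directly with health care professionals and, in phase I, a coordinator who acts as coach. Either could raise ratings of provider support while motivation stays where it was. A higher HCCQ score in the intervention group is thus compatible both with more motivation and with no change in it.

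5. **Search for another measure of motivation.**
   - The other questionnaires described under Outcome Measures cover quality of life, illness perception, anxiety and depression, and health and eHealth literacy. None is described as measuring motivation.
   - Self-determination is listed in Statistical Analysis, but no instrument is described for it and Table 1 has no row of that name.
   - The interviews are coded with inspiration from self-determination theory, but Table 1 lists patients' experiences for the intervention group only. They can inform on motivation there but give no comparison between groups.

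6. **Extent.** Table 1 has seven secondary rows: clinical data, illness perception, type of motivation, anxiety and depression, health and eHealth literacy, patients' experiences, and economic evaluation. One of the seven is mislabelled, and with it both follow-up comparisons, at 6 and 12 months.

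**The case against.** The best defence is that the choice is not arbitrary. By the article's own theory, autonomy and support from others are conditions for intrinsic motivation, so perceived autonomy support is a sensible thing to measure in this trial. The article says openly what the scale records, and a careful reader can interpret the score correctly. The outcome is secondary, and neither the sample size nor the primary outcome depends on it. All of this stands. It limits the seriousness of the point, but it does not make a rating of providers into a measure of type of motivation.

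Four stronger readings are tempting, and the document does not support them.

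- **That the scale's referent shifts** from ward staff at baseline to different teams in the two arms later. The article says only that patients rate their health care providers and does not report the instructions given. Health care center staff are also involved in the intervention arm: phase II may take place at a health care center, and its professionals have access to the data.
- **That change from baseline must therefore be abandoned** and baseline used only as a covariate. This rests on the supposed shift. Even if there were one, randomised arms share a common baseline, so the difference in change and the difference in follow-up score target the same contrast. Adjustment affects precision, not what the scale measures.
- **That self-determination should simply be deleted.** It is listed among outcomes acquired by questionnaire, and a condensed article may not describe every questionnaire. Deleting an outcome that is already being collected would create a reporting problem of its own.
- **That increased motivation is a planned conclusion.** It is one item in a list of expected outcomes, not a prespecified inference.

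**Conclusion.** The point holds as a mismatch between an outcome's label and its instrument, visible within a single section of the article. An HCCQ difference would be evidence about perceived autonomy support. Alone, it could not show that motivation increased or that its type changed.

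The size is modest: one secondary outcome at two follow-up times, and one item among the expected outcomes. The correction is still worth making because it changes what the trial may claim about the mechanism it is built on.

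The conclusion rests on taking the article's description of the HCCQ as accurate; the source cited for the scale was not available. It also assumes that no other questionnaire on motivation is being collected. If the self-determination entry refers to one, motivation might be supported from that source, but the label on the HCCQ outcome would still be wrong.

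**What to change.** - Rename the outcome perceived autonomy support (HCCQ) under Type of Motivation, in Table 1 and in Statistical Analysis, and carry the name through to the abstract's list of secondary outcomes.
- In the abstract and the Conclusions, limit the claim expected from this scale to perceived autonomy support. Motivation can still be explored in the planned interviews, without a comparison between groups.
- Reconcile self-determination in Statistical Analysis. If a questionnaire for it is being collected, name it and add it to Table 1. If not, drop it from the list of analysed outcomes.

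The changes are to wording and need no new data. The price is that one expected claim becomes narrower. Adding a motivation questionnaire now is the less practical route: enrollment began in December 2016, and baseline values for patients already enrolled could not be recovered.
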